### Data collection

Pre-hospital data of trauma patients is routinely collected by EMS professionals through digital run-reports. Extra variables, mainly answers to the questionnaire and usage information, will be collected by the TTApp in the intervention period. Clinical data, including all relevant patient outcomes, of all patients admitted to one of the participating hospitals will be collected through the trauma registries of each inclusive trauma region. Injury Severity Scores will be routinely calculated within 30 days after the date of injury by trained trauma registrars for all admitted patients and those who die in the emergency department. All other included patients are assumed to have minor or moderate injuries (ISS < 16). This assumption was validated for all patients discharged from the emergency department in a previous study [6]. Hospital data and pre-hospital data will be anonymized first, and then linked using a combined deterministic and probabilistic linkage scheme. This anonymized linkage approach was validated to be both highly sensitive and specific in prior research [6]. The final dataset will be accessible by [name], [name], and MP.

### Patient safety

The TTApp is a diagnostic intervention aimed at EMS professionals. Regular care by EMS professionals should not be impacted by the TTApp. The prediction model is a decision support tool that—alike the NPAS—can be overruled by EMS professionals. This model is more sensitive and less specific compared to the NPAS, meaning that severely injured patients have a higher chance to get an advice for transportation to a higher-level trauma center. It will not be mandatory for EMS professionals to use the TTApp during the intervention period.

### Primary outcome

Primary endpoint of the study is undertriage, defined as the transportation of a severely injured patient (ISS ≥ 16) transported from the scene of injury to a lower-level trauma center. This implies that on patient level, a severely injured patient can be either correctly triaged and transported to a higher-level one trauma center or incorrectly triaged and transported to a lower-level trauma center.

### Secondary outcomes

Overtriage, defined as the transportation of non-severely injured patients (ISS < 16) from the scene of injury to a higher-level trauma center, will be evaluated on patient level.A non-compliance analysis will be conducted to evaluate the efficacy of the TTApp under ideal circumstances with complete adherence by all EMS professionals in the specified study population.Use of health care resources. A comparative analysis will be performed to evaluate the differences in hospital length of stay, number of admissions to the Intensive Care Unit, and length of stay at the Intensive Care Unit, between control and intervention conditions.The diagnostic accuracy of the prediction model incorporated in the TTApp will be evaluated for all eligible patients.A cost-effectiveness analysis will be performed alongside this SW-CRT that is described in a separate protocol.

### Statistical analyses

#### Primary analysis

The primary endpoint—undertriage—will be analyzed at a patient level using a generalized linear mixed model (GLMM). A random intercept will be introduced in the model to account for cluster differences. Time will be modeled as a categorical variable denoting the cluster step. The GLMM will be used in conjunction with the binomial distribution and the identity link, resulting in a risk difference between the control and intervention condition. A small sample correction will be applied owing to the small number of clusters [9, 10]. Bootstrapped 95% CIs will be estimated from this model. This intention-to-treat analysis will be adjusted for age, which is expected to be non-linear and thus will be modeled using restricted cubic regression splines. In addition, we will estimate relative risks and corresponding confidence intervals using a log-binomial GLMM. Missing values will be multiply imputed using a multilevel multiple imputation strategy using chained equations which accounts for cluster differences using the R package micemd [11]. All statistical analyses will be conducted in R (version 3.6.2; R Foundation for Statistical Computing) [12].

### Secondary analyses

Overtriage is analyzed using the same strategy as the primary analysis: a GLMM using a binomial distribution and the identity link resulting a risk difference. Bootstrapped 95% CIs will be calculated, and analyses will be adjusted for age. All statistics are calculated for patients with an ISS < 16.The primary analysis is aimed to assess the effectiveness of the TTApp. A non-compliance analysis, using instrumental variable estimation, will be conducted to evaluate the efficacy of the TTApp in the hypothetical situation with complete adherence [13, 14].Healthcare resources measured on a continuous scale (e.g., length of stay) are analyzed using a GLMM with a Gaussian distribution and the identity link. Numbers of admissions are converted to proportions and analyzed similar to the primary analysis.The probability generated by the logistic regression model incorporated in the TTApp will be calculated for all eligible patients based on the digital run-reports and the data generated by the TTApp. Diagnostic accuracy measures, such as sensitivity, specificity, predictive values, and likelihood ratios, will be calculated and model discrimination and calibration will be assessed.

#### Sample size

The primary goal of the TESLA study is to evaluate whether implementation of the TTApp in daily practice reduces undertriage. The sample size calculation is based on this endpoint. The intra-cluster correlation was calculated using the Fleiss-Cuzick method on data from studies by Voskens and colleagues and the Dutch National Trauma Registry and was 0.098 (95% CI, 0.028–0.150) [5, 6, 15]. The proportion of expected undertriage under usual care was 0.35, whereas a decrease of 0.1 was expected during the intervention period. A decrease of 0.1 was expected based on the pre-defined threshold probability of the TTApp. With eight clusters, a power of 80%, a significance level of 0.05, and two clusters switching to the intervention after every step, at least 48 severely injured patients will have to be included per cluster per step [16, 17]. The expected power given the intra-cluster correlation interval ranges from 0.79 to 0.82 [18]. Approximately 1300–1400 severely injured patients will be transported by the participating EMSs on a yearly basis; therefore, we expect a duration of (less than) 4 months per step. Patient dropout was not expected to occur [6]. The total study time consists of a baseline period plus four additional steps, totaling 20 months in which 1920 severely injured patients should be included.

Approximately 1536 severely injured patients were included until December 1, 2019, of which 576 patients were recruited during the intervention period.

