This study is limited by the fact that current population values were used to determine the sample size. These values might not reflect actual event rates during the trial. Patients require an ISS ≥ 9 to be eligible for inclusion in this trial. This is based on the assumption that EMS professionals are able to differentiate between mildly injured patients and those who are severely injured, which is likely, but might not entirely resemble actual usage. This constraint was posed to limit overtriage of a clearly non-severely injured group of patients. A second limitation is the use of an exchangeability correlation structure in the analyses. Since the design of this study, methodological literature has been moving towards more complex correlation structures (e.g., discrete time decay correlation) which might be more appropriate for stepped-wedge study designs [18]. Another potential limitation of the trial is the innovativeness of the TTApp and subsequently its dissimilarity to routinely used static decision schemes. This could potentially lead to substantial nonadherence. Due to these reasons and because of the fixed length of the steps in a SW-CRT and its inextensible nature, the sample size was calculated with a conservative estimate of the expected decrease in undertriage.

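### The stated 80% power (0.79 to 0.82) belongs to an uncorrected z-test with within-cluster correlation constant over 20 months; it leaves out the planned small-sample correction and any decay in correlation

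*Protocol article*

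**What the plan says.** The Sample size section sets a minimum of 48 severely injured patients for each cluster in each step, under these conditions: "With eight clusters, a power of 80%, a significance level of 0.05, and two clusters switching to the intervention after every step". The effect is given as follows: "The proportion of expected undertriage under usual care was 0.35, whereas a decrease of 0.1 was expected during the intervention period". The ICC "was 0.098 (95% CI, 0.028–0.150"), and the only uncertainty carried into power is that interval: "The expected power given the intra-cluster correlation interval ranges from 0.79 to 0.82". On duration and total: "The total study time consists of a baseline period plus four additional steps, totaling 20 months in which 1920 severely injured patients should be included".

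The Primary analysis section specifies a mixed model with a cluster random intercept and categorical time, and adds: "A small sample correction will be applied owing to the small number of clusters". The type of correction is left to two references.

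The Discussion states: "A second limitation is the use of an exchangeability correlation structure in the analyses". It adds that the literature has since moved towards structures such as discrete time decay, which might suit stepped-wedge designs better. It gives no decay value.

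**The concern.** The power sentence and the analysis section do not describe the same test. One rests on normal quantiles; the other commits to a correction because eight clusters are few. The size was set exactly at the 80% threshold, so there is no reserve to absorb a feature left out of the calculation.

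The range of 0.79 to 0.82 also reads as a robustness statement, but it varies only the ICC. In a stepped wedge with constant correlation, power hardly depends on the ICC. It depends much more on how far correlation within a cluster falls between periods, and that is held at no fall at all. The article names this structure as a limitation of the analysis but does not connect it to the power figure.

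The Discussion itself says that the step lengths are fixed and the design cannot be extended, so a shortfall could not be repaired later. A non-significant result would be read against a nominal 80%.

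**Working it through.** **Inputs (Sample size section).** I = 8 clusters, T = 5 periods, two clusters switching per step, m = 48 per cluster-period (8 × 5 × 48 = 1920), risk 0.35 falling to 0.25, ICC 0.098 (0.028 to 0.150), alpha 0.05 (taken as two-sided). Assumption: total variance is the mean of the two binomial variances, (0.35 × 0.65 + 0.25 × 0.75)/2 = 0.2075.

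**Formula (Hussey-Hughes).** With s = (1 − ICC) × 0.2075/m and b = ICC × 0.2075,

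Var = I·s·(s + T·b) / [(I·U − W)·s + (U² + I·T·U − T·W − I·V)·b].

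The numbers of treated clusters per period are 0, 2, 4, 6, 8, so U = 20 and W = 120. The treated periods per cluster are 4, 3, 2, 1 (two clusters each), so V = 60. The brackets are 160 − 120 = 40 and 400 + 800 − 600 − 480 = 120.

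**Step 1: reproduce the stated power.** At ICC 0.098, s = 0.003899 and b = 0.020335.
- Var = 8 × 0.003899 × 0.105574 / (40 × 0.003899 + 120 × 0.020335) = 0.003293/2.5962 = 0.001269, so SE = 0.0356.
- Power = Φ(0.10/0.0356 − 1.96) = 0.802.
- At ICC 0.028 and 0.150 it is 0.795 (0.7945 before rounding) and 0.821.
- With 47 per cluster-step, power at ICC 0.098 is 0.794, so 48 is the minimum for 80%.

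The stated 80% and 0.79 to 0.82 are therefore those of the uncorrected z-test with constant correlation.

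**Step 2: add a small-sample correction, correlation still constant.** The SE is unchanged and the reference is a noncentral t. The df are assumptions: 6 = clusters − 2; 27 = 40 cluster-periods − 8 clusters − 4 period contrasts − 1 treatment term. The stated accrual of 1300 to 1400 a year gives 1300/3/8 = 54 to 1400/3/8 = 58 per cluster-step.

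| ICC 0.098 | z | 27 df | 6 df |
|---|---|---|---|
| 48 per cluster-step | 0.80 | 0.77 | 0.65 |
| 54 per cluster-step | 0.84 | 0.82 | 0.70 |
| 58 per cluster-step | 0.87 | 0.84 | 0.73 |

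A patient-level Satterthwaite df (about 750 to 1850 across the ICC interval) leaves power near 0.80 at 48. For 80% at ICC 0.098, 27 df would need 52 per cluster-step (2080 in total) and 6 df would need 70 (2800).

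**Step 3: let correlation fall between periods (z-test, 48 per cluster-step).** Replace b by CAC × b and s by s + (1 − CAC) × b. For example, at ICC 0.098 and CAC 0.90, s = 0.003899 + 0.002034 = 0.005933 and b = 0.018302. Then SE = 0.0436 and power = Φ(2.294 − 1.96) = 0.63. The CAC values are assumptions.

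| CAC | ICC 0.028 | ICC 0.098 | ICC 0.150 |
|---|---|---|---|
| 1 | 0.79 | 0.80 | 0.82 |
| 0.95 | 0.77 | 0.71 | 0.68 |
| 0.90 | 0.75 | 0.63 | 0.57 |
| 0.80 | 0.71 | 0.52 | 0.43 |

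At CAC 1 a higher ICC raises power slightly; below 1 it lowers it. The difference detectable with 80% power at ICC 0.098 is (1.96 + 0.842) × SE: 0.100 at CAC 1, 0.122 at 0.90 and 0.140 at 0.80.

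**Step 4: what the planned model would do.** The figures in step 3 are for a test with valid standard errors. If correlation decays but the random-intercept model is fitted, its standard error is too small. At ICC 0.098, the true SE is 1.18 times the model-based one for a decay of 0.95 per step, and 1.33 times for 0.90. The harm then appears as inflated type I error.

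**The case against.** The strongest reply is that nothing is miscalculated. The figures are right for their inputs, and the sentence says its range is conditional on the ICC interval. That stands: this is not an arithmetic error. The calculation and the planned model also share the exchangeable structure, and the article discloses that structure as a limitation.

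A reader might infer that the article concedes decay in this trial and hence power of about 0.5 to 0.6. The text does not support this. It makes a general remark that other structures might be more appropriate, gives no value, and does not say that decay is expected here. At ICC 0.028, inside the article's own interval, CAC 0.90 costs only about 5 points.

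A reader might also infer that the correction brings power down to 0.65. That holds only on 6 df. The article does not name the method and says that confidence intervals are bootstrapped, so the loss at 48 per cluster-step runs from almost none, through 3 points, to 15. At the expected accrual, the 27 df version exceeds 0.80 with constant correlation. The stated target nevertheless remains 48 per cluster-step and 1920 in total.

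The claim in the Discussion that the effect estimate is conservative does not offset the point, because the Sample size section presents 0.1 as the decrease expected from the app's threshold. Nor does the point depend on details usually left to an analysis plan: both the power figure and the features it omits are stated in this article.

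**Conclusion.** The point holds at moderate importance. The stated 80% (0.79 to 0.82) describes an uncorrected z-test with CAC = 1, sized with no margin, while the article commits to a corrected test. With constant correlation at ICC 0.098, the corrected test has power between 0.65 and nearly 0.80 at 48 per cluster-step, depending on a correction the article does not identify. At 54 to 58 per cluster-step it is 0.70 to 0.73 on 6 df or 0.82 to 0.84 on 27 df.

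The narrowness of the range follows from fixing CAC at 1 and is not evidence of robustness. How much lower power would be under decay cannot be settled from the article. The CAC grid shows sensitivity under assumed values and refers to a valid test, not to the random-intercept model as planned. All figures assume a two-sided test, equal cluster-period sizes and variance 0.2075.

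**What to change.** Keep the sample size and change the text of the Sample size section:

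1. State that 80% (0.79 to 0.82) applies to the uncorrected test with within-cluster correlation constant over all five periods.
2. Restate power for the small-sample-corrected test actually planned, at 48 per cluster-step and, if wished, at the expected 54 to 58.
3. Add a grid over ICC 0.028, 0.098, 0.150 and CAC 1, 0.95, 0.90, 0.80, labelled as assumption-based, with the detectable difference at ICC 0.098 (z-test: 0.100 at CAC 1, 0.122 at 0.90, 0.140 at 0.80).
4. Link the grid to the limitation in the Discussion, and note there that fitting the exchangeable model under decay would understate standard errors.

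The cost is a few sentences and a small table. No patients are added and the analysis does not change. The drawback is that the published power becomes less favourable. About 1536 of the 1920 patients were already included by December 2019, so the change serves the interpretation of the result, not recruitment.

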## Discussion

Getting the right patient to the right hospital within a certain time frame is becoming increasingly important with the maturation of trauma systems and centralization of resources. Costs and mortality rates can be reduced by minimizing undertriage, overtriage, and interhospital transfer rates. The optimal hospital for an individual injured patient has to be determined on-scene by a diagnostic strategy that consists predominantly of (1) identification of injured patients in need of specialized trauma care and (2) logistical considerations, such as trauma center proximity and trauma center capacity. Pre-hospital triage tools, such as the Field Triage Decision Scheme, the NPAS, and the TTApp, attempt to assist EMS professionals in the first step of this strategy. These diagnostic tools should be thoroughly tested and preferably evaluated by both external validation and impact assessment before widespread implementation in clinical practice. External validation is crucial to evaluate the true performance of a prediction model in new (external) patients. Although the previously described prediction model is externally validated already, the application of the study results in practice might uncover implementation problems, disadvantages of a digital approach, and possible improvements and might thus yield different results than expected. The aim of the TESLA trial is therefore to assess the impact of the TTApp in practice. This will likely give insights into reasons for nonadherence, reasons to overrule the prediction model and its advice, and the isolated impact of many of the components in the diagnostic strategy that lead to the determination of the most optimal hospital.

Individual randomization of patients was not deemed appropriate during field triage, especially in time-critical settings. A stepped-wedge cluster-randomized design was chosen to mitigate logistical constraints such as labor intensity (e.g., training of EMS professionals) through phased implementation of the intervention and enabled all participating EMSs to evaluate the TTApp. Stepped-wedge cluster-randomized designs are particularly used to evaluate the impact of the implementation of prediction models in clinical practice [19]. This unidirectional crossover design combines elements of before-after studies with cluster randomization and is an efficient design that enables to derive a valid answer for the research question.

This study is limited by the fact that current population values were used to determine the sample size. These values might not reflect actual event rates during the trial. Patients require an ISS ≥ 9 to be eligible for inclusion in this trial. This is based on the assumption that EMS professionals are able to differentiate between mildly injured patients and those who are severely injured, which is likely, but might not entirely resemble actual usage. This constraint was posed to limit overtriage of a clearly non-severely injured group of patients. A second limitation is the use of an exchangeability correlation structure in the analyses. Since the design of this study, methodological literature has been moving towards more complex correlation structures (e.g., discrete time decay correlation) which might be more appropriate for stepped-wedge study designs [18]. Another potential limitation of the trial is the innovativeness of the TTApp and subsequently its dissimilarity to routinely used static decision schemes. This could potentially lead to substantial nonadherence. Due to these reasons and because of the fixed length of the steps in a SW-CRT and its inextensible nature, the sample size was calculated with a conservative estimate of the expected decrease in undertriage.

## Conclusion

The TESLA trial is a SW-CRT that aims to evaluate the impact of the TTApp on the primary endpoint undertriage, as well as overtriage and hospital resource use. The smartphone application can potentially acquire new and previously undiscovered insights into several components of the strategy that leads to the determination of the optimal hospital for a specific injured patient.

## Data Availability

Study results will be disseminated via a peer-reviewed international medical journal. Designated authors have to meet all four criteria for authorship in the International Committee of Medical Journal Editors (ICMJE) recommendations.

## Abbreviations

EMS: Emergency Medical Services
NPAS: National Protocol of Ambulance Services
TTApp: Trauma Triage App
TESLA: Trauma Triage using Supervised Learning Algorithms
SW-CRT: Stepped-wedge cluster-randomized trial
ISS: Injury Severity Score
GLMM: Generalized linear mixed model
